#### Procedures for recording and reporting adverse events

These details are outlined in Additional file 3.

#### Adverse events that do not require reporting

These will include the following:

1) Symptoms due to aeroallergen exposure i.e. nasal blockage, rhinorrhea, itching or sneezing; Itching, watering redness or swelling of eyes; itching or dryness of mouth/throat; breathless, cough, wheeze and chest tightness.

2) Transient discomfort from intradermal injections.

3) Appearance of an itchy oedematous wheal with surrounding erythema (early response) after intradermal injection.

4) Appearance of swelling (oedema) within hours of intradermal injection, that may persist for several days (late response). These responses may be associated with very mild local tenderness.

5) Temporary discomfort,, bleeding, bruising, swelling at the needle site following venesection, and in rare instances, infection. Some people may experience lightheadedness, nausea, or fainting.

6) Mild localised itching arising from skin prick testing during screening.

#### Treatment stopping rules

The trial will be stopped in the event of five grade 3 reactions or a single grade 4 reaction. In addition the trial may be prematurely discontinued by the Sponsor, Chief Investigator or Regulatory Authority on the basis of new safety information or for other reasons given by the Data Monitoring & Ethics Committee/Trial Steering Committee regulatory authority or ethics committee. The trial may also be prematurely discontinued due to lack of recruitment or upon advice from a Trial Steering Committee who will advise on whether to continue or discontinue the study and make a recommendation to the sponsor. If the study is prematurely discontinued, participants will be informed and no further participant data will be collected.

#### Code breaking

24 hr Emergency Code Break and Medical Information will be provided by Guy’s & St Thomas’ NHS Foundation Trust Emergency Scientific Medical Services (eSMS). Each randomised subject will be provided with a card detailing code break telephone numbers and emergency contact details. Subjects will be requested to carry this card with them at all times whilst participating in the trial.

### Study data

#### Data handling

The Chief Investigator will act as custodian for the trial data. The following guidelines will be strictly adhered to:

•Patient data will be anonymised.

•All anonymised data will be stored on a password protected computer.

•All trial data will be stored in line with the Medicines for Human Use (Clinical Trials) Amended Regulations 2006 and the Data Protection Act and archived in line with the Medicines for Human Use (Clinical Trials) Amended Regulations 2006 as defined in the King’s Health Partner’s Clinical Trials Office Archiving SOP.

#### Data management

Data will be managed using the InferMed MACRO database system. An electronic Case Report Form (eCRF) will be created using the InferMed Macro system. This system is regulatory compliant (GCP, 21CRF11, EC Clinical Trial Directive). The eCRF will be created in collaboration with the trial statisticians and the CI and maintained by the King’s Clinical Trials Unit. It will be hosted on a dedicated secure server within KCL. Source data will be entered by authorised staff onto the eCRF with a full audit trail.

#### Database passwords

Database access will be strictly restricted through passwords to the authorised research team. The CI or delegate will request usernames and passwords from the KCTU. It is a legal requirement that passwords to the eCRF are not shared, and that only those authorised to access the system are allowed to do so. If new staff members join the study, a personalised username and password will be requested via the CI or delegate.

#### Data handling & confidentiality/format of records

Data will be handled, computerised and stored in accordance with the Data Protection Act, 1998. Participants will be identified on the study database using a unique code and initials. The investigator will maintain accurate patient records/results detailing observations on each patient enrolled.

#### Identifiable data

All participant contact information data will be stored on spreadsheets within the recruiting NHS site, which will have restricted access from password protected computers. Accrual data uploaded to the UKCRN portfolio database will be anonymised and collated by the CI or delegate to the CLRN. No identifiable data will be entered on the eCRF or transferred to the KCTU.

#### Main database

SAE data will be collected on paper SAE report forms and faxed to the KHPCTO. Summary details of SAEs will be transcribed to adverse event section of the eCRF. For all other data collected, source data worksheets will be prepared for each patient and data will be entered onto the eCRF database. Source data worksheets will be reconciled at the end of the trial with the patients NHS medical notes in the recruiting center. During the trial, critical clinical information will be written in the medical notes to ensure informed medical decisions can be made in the absence of the study team. Trial related clinical letters will be copied to the medical notes during the trial. The Chief Investigator will provide an electronic signature for each patient Case Record Form once all queries are resolved and immediately prior to database lock.

At the end of the study, essential documentation will be archived in accordance with sponsor and local requirements. The retention of study data will be the responsibility of the Chief Investigator. Any data exports (other than baseline data) will require authorisation by the trial statistician.

#### Statistical analysis

The Statistical Analysis Plan will be finalised by the trial statistician and approved by the TSC and the DMEC prior to database lock. The study will be unblinded after the final intradermal injection in September 2014. No interim analysis is planned although pre-defined stopping criteria will be discussed by the TSC and the Independent DMEC and agreed if appropriate. Descriptive statistics will be produced for DMEC reports and in the primary analysis. For each of the variables analysed, univariate descriptive statistics will be summarised by randomised group to provide an overview of the data. Summary measures for the baseline characteristics of each group will be presented as mean and standard deviation for continuous (approximate) normally distributed variables, medians and interquartile ranges for non-normally distributed variables, and frequencies and percentages for categorical variables. The Area under the Curves (AUC) of the combined symptom and medication scores for the period corresponding to the grass pollen season (mid May-Aug) will be plotted against time as a summary measure of the primary outcome. This will provide each patient’s longitudinal outcome as a single quantity, which will be calculated for Symptom and Medication scores. The planned primary efficacy analysis i.e. the difference between the two arms in AUC of the combined symptom and medication scores, will be analysed on randomised patients using (stratified) Mann–Whitney *U* test (Van Elteren test statistic), adjusted for the baseline stratification factors (size of the skin test to grass pollen and presence or absence of rhinitis symptoms outside the grass pollen season). Sample size estimation assumed 10% of patients would not provide evaluable end of study information. If this rate is observed, multiple imputation methods will be used in order to provide an overall treatment effect estimate with a standard error that is properly inflated to incorporate uncertainty associated with imputing values. Since this may introduce a bias if the main reason for drop-out was deterioration, a sensitivity analysis will be performed to explore departures from the ‘missing at random’ assumption. Similar analyses will be conducted for secondary (symptom scores, medication scores and individual symptoms) and mechanistic outcomes. Regression models will be also used to evaluate the change in RQLQ scores to isolate the effect of the intervention on each arm after adjusting for stratification factors. In analyzing the recovery of the cutaneous late response at each 3, 6 and 12 month time point, the size of late response in the group that originally received active therapy will be compared with the group that originally received the control intervention. As a further sensitivity analysis, all key outcomes will be re-analysed adjusting for any observed differences at baseline that are judged to be of clinical importance. Differences between the groups will be estimated with 95% confidence intervals. The principal software package will be SAS, with verification of results from syntax for selected analyses analysed in STATA.

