### Secondary endpoints in mechanistic assays

1) Inflammatory cells (eosinophils, mast cells, basophils, CD4+ T cells and Foxp3+ T cells) in skin biopsies collected 24 hours after receiving an intradermal diluent (negative control) and grass pollen allergen injection in September 2013.

2) Numbers of CRTH2^pos^CD203c^pos^CD3^neg^CD303^neg^ and CRTH2^pos^CD63^pos^CD3^neg^CD303^neg^ activated peripheral blood basophils cells following in vitro activation with grass pollen allergen (Visit 7).

3) Serum concentrations of *Phleum pratense*-specific IgG, IgG1, IgG4 and IgE at Visit 1 and Visit 7. These sera will also be tested for inhibitory activity against allergen-IgE complex binding to B cells.

4) Gene expression profiles of CD4+ T cells derived from skin biopsy explants in September 2013.

5) Cutaneous allergen-induced late response size measured in December 2013 (i.e. approx. 3 months after previous intradermal injection), March 2014 (6 months) or August 2014 (11–12 months).

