### Recruitment

Participants for PollenLITE will be identified via a recruitment campaign including advertisements in press, online and on public transport. Potential participants will be invited to visit the trial website (http://www.pollenlite.co.uk) and answer 7 pre-screening questions before registering. Participants passing pre-screening on the trial website will be contacted for further telephone screening, and if considered potentially suitable will be invited to attend the Clinical Research Facility at Guy’s Hospital for a formal screening visit. A Participant Information Sheet will be provided to each person to read prior to the screening visit. At the screening visit (Visit −1), there will be an opportunity to ask questions of a staff member trained in all trial procedures, as formally delegated by the PI. Written informed consent will be obtained by a physician prior to screening and any other study specific procedures taking place. The original signed consent form will be retained in the Investigator Site File, with a copy filed in the participant’ s hospital records, and a further copy provided to the participant. Individuals will be free to decline further participation without giving reasons. The screening visit will comprise a full medical and allergic history, skin prick testing to a panel of common inhalant allergens, recording of concomitant medications, limited physical examination, measurement of vital signs, spirometry and collection of a venous blood sample for total and *Phleum pretense*-specific IgE levels and for storage for serum based mechanistic assays (baseline sample). For participants who either do not meet the eligibility criteria at the screening visit or decline to proceed further, reasons for non-participation will be recorded where known. The history and test results of every potentially eligible participant will be reviewed by the PI before an appointment is made for Visit 1 (randomisation and first injection). To ensure that a minimum of 90 participants is randomised, up to 100 screened participants will be booked for visit 1, allowing for a 10% drop-out rate between screening and randomisation. In the event that more than 90 eligible participants attend for visit 1, all will be included in the study and randomised up to a maximum of 100. All female participants of childbearing age will be required to undergo a urine pregnancy test with sensitivity of less than 50 mIU/mL within 72 hours of randomisation and first administration of study therapy at Visit 1.

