The persistence of late response suppression will be evaluated by randomising active and control subjects in Aug 2013 into 3 groups. Each group will receive a follow-up intradermal injection of 10 BU (33.3 SQ-U) of grass pollen allergen, as well as a diluent control injection, at either 3, 6 or 12 months. Reversal of late response suppression will be assessed at each time point by comparing mean late response size in the active and control groups.

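### Mechanistic outcomes inherit the primary's stratified rank test, which gives no role to the pre-treatment serum values already collected: a minor loss of precision, not a bias

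*Protocol article*

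**What the plan says.** All references are to the protocol article.

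- **Statistical analysis.** The primary comparison of combined-score AUC uses a stratified Mann–Whitney test ("Van Elteren test statistic), adjusted for the baseline stratification factors"). The factors are grass skin-test size and whether rhinitis occurs outside the season. The section continues: "Similar analyses will be conducted for secondary (symptom scores, medication scores and individual symptoms) and mechanistic outcomes". The following sentence models change for the RQLQ. No such wording is given for the serum or biopsy outcomes.
- **Secondary endpoints in mechanistic assays, item 3.** *Phleum*-specific antibodies are measured as "IgG, IgG1, IgG4 and IgE at Visit 1 and Visit 7", and the same sera are tested for inhibition of allergen-IgE binding to B cells.
- **Recruitment.** Blood is drawn at screening for IgE and "for storage for serum based mechanistic assays (baseline sample").
- **Secondary endpoints in mechanistic assays, item 1.** Inflammatory cells are counted "in skin biopsies collected 24 hours after receiving an intradermal diluent (negative control) and grass pollen allergen injection in September 2013".
- **Statistical analysis, safeguards.** The SAP is to be finalised before database lock. A sensitivity re-analysis of key outcomes will adjust for baseline differences that are observed and judged clinically important.

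**The concern.** The primary outcome is one AUC per person with no pre-treatment counterpart, so a two-arm stratified rank test suits it. The serum outcomes have a different structure: each participant has a value before treatment and one at Visit 7. Carrying the primary's method across leaves open whether the Visit 7 level or the change is ranked, and it names no use for the pre-treatment value.

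If the Visit 7 level alone is compared, stable differences between people in specific IgE and IgG stay in the error term. Secondary objective 3 (mechanism) rests partly on these comparisons, with about 40 evaluable participants per arm. What is at stake is the size of antibody shift the trial can detect. The validity of the test is not in question.

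**Working it through.** **1. The plan's own figure.** The Sample size calculation section starts from 35 per arm, adds 15% (35 × 1.15 = 40.25, stated as 40), then allows for 10% dropout: 40 / 0.9 = 44.4, so 45 per arm and 90 in total. The steps from 35 to 90 reproduce. The 35 itself rests on raw data from an earlier trial that are not shown. No power is stated for any mechanistic outcome, so nothing here touches the 90.

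**2. Inputs for the serum comparison.**
- n = 40 evaluable per arm, from that section.
- Two-sided 0.05, as in that section. The 80% power is a convention chosen here.
- Correlation ρ between the pre-treatment and Visit 7 values, within strata and on the analysis scale. The documents do not give it, so it is an assumption, run from 0.3 to 0.9.

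**3. Formulas.** In SD units of the Visit 7 value, the variance factor is 1 for the Visit 7 value alone and 1 − ρ² for ANCOVA on the pre-treatment value. The detectable difference is (1.960 + 0.842) × √(2 × factor / n). With no adjustment and n = 40 this is 2.802 × √(2/40) = 0.63 SD.

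| ρ (assumed) | 1 − ρ² | Variance cut | Detectable difference (SD) |
|---|---|---|---|
| no adjustment | 1.00 | – | 0.63 |
| 0.3 | 0.91 | 9% | 0.60 |
| 0.5 | 0.75 | 25% | 0.54 |
| 0.7 | 0.51 | 49% | 0.45 |
| 0.9 | 0.19 | 81% | 0.27 |

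**4. Check with the test actually planned.** This was simulated with normal data, four strata, 40 per arm and 2,000 runs per setting, at a true difference of 0.63 SD.

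| ρ | Van Elteren, Visit 7 value | Van Elteren, change | ANCOVA |
|---|---|---|---|
| 0.3 | 0.77 | 0.62 | 0.83 |
| 0.5 | 0.75 | 0.75 | 0.89 |
| 0.7 | 0.76 | 0.93 | 0.97 |
| 0.9 | 0.75 | 1.00 | 1.00 |

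Normal data slightly favour ANCOVA: at ρ = 0 its power is 0.78 against 0.76 for the rank test. The rest of the gap comes from the baseline value. With no true difference, rejection rates for all three methods lay between 0.039 and 0.055, so none is biased.

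**5. Ranking the change is not a safe default.** Its variance factor is 2(1 − ρ), which is below 1 only when ρ exceeds 0.5. At ρ = 0.3 it is 1.4, and simulated power falls from 0.77 to 0.62. ANCOVA's factor never exceeds 1.

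**6. Biopsies.** The Randomisation section gives 40 biopsied participants in total; 20 per arm is an assumption. Using the allergen site alone, the detectable difference is 2.802 × √(2/20) = 0.89 SD. For an allergen-minus-diluent difference it is 1.05, 0.89, 0.69 and 0.40 SD at between-site correlations of 0.3, 0.5, 0.7 and 0.9. The choice can help or hurt, so it should be fixed beforehand. The diluent site is sampled in September 2013, after treatment. It is therefore not a baseline, and its use as a covariate is debatable.

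**The case against.** The strongest reply is that this belongs to the SAP. The article says an SAP will follow, it condenses a fuller protocol, and covariates for laboratory endpoints are commonly settled later. That would answer a complaint of missing detail. It does not fully answer this one, because the article states a method for these outcomes and that method comes from an outcome without a baseline.

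A reader might infer four stronger things that the documents do not support.

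- **That the plan compares post-treatment levels only.** The text says the analyses will be similar, not identical. Ranking a change or an allergen-minus-diluent difference would fit it. The most that can be said is that the stated method assigns these values no role.
- **That most of the precision is thrown away.** More than half the variance is removed only if ρ² exceeds 0.5, that is ρ above about 0.71. Skin-test stratification may already absorb some between-person variation in IgE. The interval also matters: it is about 12 weeks from Visit 1, but longer from screening, since the Sample size calculation section places recruitment several months before Visit 1.
- **That all mechanistic outcomes are affected.** Basophil activation is listed at Visit 7 only, gene expression has no listed comparator, and the late response has its own analysis sentence.
- **That the result would be biased.** The simulated error rates show otherwise.

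The planned sensitivity analysis helps little. It is triggered by observed imbalance and limited to key outcomes, so it is not prespecified adjustment for precision. It is fair to say that ANCOVA adds model assumptions the rank test avoids; a log or rank scale and a retained rank test meet that.

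**Conclusion.** The point holds for the serum outcomes, as a minor one. The stated method gives no role to a pre-treatment value that is already collected. Depending on an assumed correlation of 0.3 to 0.9, using that value would cut the variance by 9% to 81% and lower the detectable difference from 0.63 SD to between 0.60 and 0.27 SD with 40 per arm. At the low end the gain is small. The figures rest on approximate normality on the analysis scale and on 40 evaluable sera per arm. For biopsy cell counts, the conclusion is only that the role of the diluent site should be stated. The primary analysis and the sample size of 90 are untouched.

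**What to change.** In the SAP, before database lock:

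1. State that Visit 7 *Phleum*-specific IgG, IgG1, IgG4, IgE and IgE-blocking activity are compared between arms by ANCOVA, on a log or rank scale, with the participant's pre-treatment value and both stratification factors as covariates.
2. Keep the stratified rank test as a sensitivity analysis.
3. Reconcile which sample is the baseline: the Recruitment section labels the screening serum as baseline, while the mechanistic endpoint list names Visit 1.
4. For biopsy cell counts, state how the same participant's diluent site enters the comparison, for example as the allergen-minus-diluent contrast.

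The cost is a few lines of SAP text. The values are already scheduled for collection, so no new samples, visits or participants are needed.

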
#### Sample size calculation

Power calculations for the primary outcome (combined symptom and medication score) were performed based on raw data from a previous clinical trial of subcutaneous grass pollen immunotherapy [29]. The power calculation has been conservatively based on the detection of a clinical effect size 80% of that reported in that trial. Using this method and a two-sided non-parametric test based on a Monte Carlo approach, group sample sizes of 35 and 35 achieve 90% power to detect such difference in AUC of the combined symptom and medication scores at a significance level of 0.05. To make allowance for the unknown distribution of the primary outcome and based on the lower bound for the asymptotic relative efficiency (ARE) of the Mann–Whitney *U* test, we have increased the sample size by a further 15% to 40 in each arm. Further accounting for a post-randomisation dropout rate of up to 10% consistent with previous trials of grass pollen immunotherapy, a total sample size of 90 (45 each arm) is required. Recruitment will take place several months before visit 1. At visit 1 randomisation will be performed and the first injection administered. To ensure that a minimum of 90 participants is randomised, up to 100 screened participants will be booked for visit 1, allowing for a 10% drop-out rate between screening and randomisation.

## Discussion

This protocol will allow us to test our hypothesis that low dose intradermal immunotherapy with grass pollen allergen is an effective treatment in seasonal allergic rhinitis caused by grass pollen. The first participant was randomised in February 2013 and the last participant is expected to complete the trial protocol in August 2014.

## Abbreviations

AE: Adverse event; AR: Adverse reaction; CI: Chief investigator; DMEC: Data monitoring committee; DSUR: Development safety update reports; eCRF: Electronic case record form; eSMS: Emergency scientific & medical services; EudraCT: European union drug regulating authorities clinical trials; FEV1: Forced expiatory volume; GCP: Good clinical practice; IgE: Immunoglobulin E; IMP: Investigational medicinal product; ISRCTN: International standardized randomised controlled trial number; KCL: King’s college london; KCTU: King’s clinical trials unit, King’s college london (UKCRC registered KCTU); KHP-CTO: Kings health partners clinical trials office (function of the sponsor); MHRA: Medicines & healthcare products regulatory agency; NIHR: National institute for health research; NRES: National research ethics service; PEF: Peak expiratory flow; PollenLITE: Pollen Low dose Intradermal Therapy Evaluation; REC: Research ethics committee; SAE: Serious adverse event; SAR: Serious adverse reaction; SOP: Standard operating procedure; SPC/SmPC: Summary of product characteristics; SUSAR: Suspected unexpected serious adverse reaction; TSC: Trial steering committee; UKCRN: UK clinical research network.
